### Probiotics as a nutritional intervention strategy in preterm infants

Despite lack of consensus on methods to prevent NEC, the gut microbiome may work as a preventative target due to the potential to influence the immature gastrointestinal system in extremely preterm infants. In these infants, intestinal bacterial colonization with normal and beneficial bacterial flora (*Bifidobacteria*) is often delayed, rendering the microbiota less diverse and dominated by *Enterobacteriacea*, increasing the potential for the invasion of harmful species [38].

Probiotics are living microorganisms and adequate administration has been linked to numerous benefits, including increased stimulation of immune functions, inhibition of pathogenic bacteria, degradation and fermentation of certain foods, and production of fat-soluble vitamins [39, 40]. The effectiveness of probiotic supplementation in modifying the gut microbiome and preventing NEC and LOS has been shown in recent research; however, the evidence among extremely preterm infants is limited. Further, evidence backing the routine use of probiotics has been challenged due methodological constraints, namely inconsistencies regarding type of probiotics tested, dosage given, enteral feeding routine, intervention duration, outcome measure definition, and general heterogeneity between studies, rendering it difficult to draw sound conclusions on effectiveness [28, 41, 42]. Nevertheless, the recent position paper, “*Probiotics and Preterm Infants*” by the European Society for Paediatric Gastroenterology, Hepatology and Nutrition (ESPGHAN), conditionally recommended probiotic supplementation in infants with birth weight <1500 g if certain safety measures are achieved [15]. The committee recommended providing either *L. rhamnosus GG ATCC53103* or a combination preparation of *Bifidobaterium infantis Bb-02*, *Bifidobacterium lactis Bb-12*, and *Streptococcus Thermophilus TH4*, the latter of which will be used in our study.

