#### Secondary aims

To determine whether probiotic supplementation will reduce the incidence of NEC.To determine whether probiotic supplementation will reduce the incidence of neonatal mortality.To determine whether probiotic supplementation will reduce the incidence of late-onset sepsis.To determine whether probiotic supplementation will reduce the rate and duration of antibiotic use during hospital stay.To determine whether probiotic supplementation will reduce duration of hospital stay.To determine whether probiotic supplementation has an effect on the development and composition of the microbiome.

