## Interventions

### Choice of probiotic {6b}

The PEPS trial will us the probiotic supplement known commercially as ProPrems®, which is comprised of a combination of one billion freeze-dried bacteria per 0.5 g in a maltodextrin base powder (*Bifidobacterium infantis Bb-02* (DSM 33361) 300 million, *Bifidobacterium lactis* (BB-12®) 350 million, and *Streptococcus thermophilus* (TH-4®) 350 million). The probiotic supplement is one of two probiotic combinations recommended by the ESPGHAN committee [15]. The product is produced by Chr Hansen in Denmark and distributed by the Swedish company Neobiomics©. The product is currently being used routinely in all Swedish hospitals for infants born in gestational weeks 28 to 32. Thus, the PEPS trial will be easy to implement considering the product is already familiar to medical and nursing staff at the participating hospitals. However, participating Danish hospitals have not implemented any probiotic supplement into clinical routine and will need to learn these routines. The control group will receive placebo produced by Chr Hansen containing 0.5 g maltodextrin powder, equivalent to the amount of maltodextrin included in the probiotic supplement.

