### Intervention description {11a}

The probiotics (intervention) or placebo (control) will be mixed with breastmilk and administered by gastric tube when infants tolerate at least 3 mL breastmilk per meal. The breastmilk may however be administered as a bolus or continuous feeds. For the intervention group, the standard dose of 0.5 g will be mixed with 3 mL breastmilk. For the control group, 0.5 g of placebo containing only maltodextrin powder will be used. If the mother’s breastmilk is available, this will be primarily used; otherwise, donated breastmilk will be given. There will be no visible difference between the breastmilk containing probiotic supplementation and placebo. The dose will be administered as the first meal of the day once daily until the infant reaches 34 weeks of gestation. The dosage and method of administration will not change with increasing age and weight. If the infant does not tolerate the enteral feeds after the start of probiotic supplementation and the administrated volume drops below 3 mL, the supplementation will be paused and started again when the infant tolerates 3 mL per meal again. If the infant does not receive the planned dose, this must be noted in the case report form (CRF). Unopened probiotic supplements and placebo will be stored at room temperature in a nutrition kitchen.

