***Secondary outcome variables***			
Late-onset sepsis	Incidence rate	Mean/Median	During study intervention (until 34 weeks of gestational age)
Verified late-onset sepsis^b^	Incidence rate	Mean/Median	During study intervention (until 34 weeks of gestational age)
Late-onset sepsis Culture-proven	Type of pathogen	Sum	During study intervention (until 34 weeks of gestational age)
Late-onset sepsis date	Date of onset	Sum	During study intervention (until 34 weeks of gestational age)
Late-onset sepsis Peripheral line at onset	Yes/No	Mean/Median	During study intervention (until 34 weeks of gestational age)
Late-onset sepsis Central line at onset	Yes/No	Mean/Median	During study intervention (until 34 weeks of gestational age)
Use of antibiotics	Rate of prescription (number) Duration of treatment (days)	Mean/Median	During study intervention and until 40 weeks of gestational age
Length of stay	Number of days	Mean/Median	Length of stay at the neonatal intensive care unit Length of stay at homecare
Effect on microbiome	Fecal samples		1. Directly after inclusion ± 2 days 2. 14 ± 2 days gestational age 3. 34 weeks ± 2 days gestational age 4. 12 months corrected age ± 2 weeks
***Serious adverse event*** (Necrotizing enterocolitis, death and late-onset sepsis included)			
Bronchopulmonary dysplasia	Yes/No	Mean/Median	During study intervention (until 34 weeks of gestational age)
Respiratory distress syndrome	Yes/No	Mean/Median	From birth and during study intervention (until 34 weeks of gestational age)
Patent ductus arteriosus (PDA)	Yes/No	Mean/Median	From birth and during study intervention (until 34 weeks of gestational age)
Pulmonary hypertension	Yes/No	Mean/Median	During study intervention (until 34 weeks of gestational age)
Intraventricular hemorrhage	Yes/No	Mean/Median	During study intervention (until 34 weeks of gestational age)
Hydrocephalus	Yes/No	Mean/Median	During study intervention (until 34 weeks of gestational age)
Retinopathy of prematurity	Yes/No	Mean/Median	During study intervention (until 34 weeks of gestational age)

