#### Primary aim 1 and secondary aims 1–3

In the initial analysis, we will compare baseline characteristics of the study population between allocation groups to ensure that balance was achieved by the randomization. We will report the mean (standard deviation [SD]) or median (first quartile, third quartile) for continuous variables, and count and percentages for categorical variables. The primary analyses will be based on the ITT population including all subjects that were randomized in the study. A crude and a multivariable-adjusted standardized logistic regression will be used to calculate the relative risk (RR) and 95% CI to estimate the effect of probiotic supplementation on the risk of NEC and/or mortality (primary aim) as well as NEC, total mortality, and LOS separately (secondary aims 1–3). The randomization will be stratified per site. Thus, the analysis will adjust for this variable before standardization. A per-protocol analysis accounting for non-compliance will also be performed. All data analyses will be performed using the STATA and R software. A two-sided *p*-value of 0.05 will be considered significant evidence of the effect of the intervention.

#### Secondary aims 4 and 5

The effect of probiotic supplementation on the rate of prescription and duration of antibiotic use during hospital stay (secondary aim 4) and duration of hospital stay (secondary aim 5) will be analyzed using standardized logistic regression and linear regression model.

#### Secondary aim 6

The effect of probiotic supplementation on gut microbiome will be investigated by comparing the alpha and beta diversity of the microbiota samples. Alpha diversity measures the mean diversity within a sample while beta diversity involves a comparison of diversities between samples and will be displayed as a principal coordinate or component analysis plot.

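### At the two stool samples taken during or at the end of dosing, the whole-sample diversity comparison for secondary aim 6 mixes product bacteria with any change in the rest of the infant's flora

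*Protocol article*

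**What the plan says.** The aim, in the protocol article under Secondary aims, is: "To determine whether probiotic supplementation has an effect on the development and composition of the microbiome". The method, in Statistical methods {20a} under Secondary aim 6, is: "The effect of probiotic supplementation on gut microbiome will be investigated by comparing the alpha and beta diversity of the microbiota samples". One further sentence explains the two measures and promises an ordination plot. Nothing there sets product strains aside or treats the sampling times differently.

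The active product holds "one billion freeze-dried bacteria per 0.5 g in a maltodextrin base powder" (Choice of probiotic {6b}), and the placebo is maltodextrin only. On duration, Intervention description {11a} states: "The dose will be administered as the first meal of the day once daily until the infant reaches 34 weeks of gestation". Dosing starts once the infant tolerates 3 mL per meal. If intake falls below that, "the supplementation will be paused and started again when the infant tolerates 3 mL per meal again".

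Table 1 and section {33} schedule stool around inclusion, at 14 ± 2 days, at "34 weeks ± 2 days gestational age" and at 12 months corrected age.

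The background says that delayed colonisation by beneficial bacteria is common in these infants, "rendering the microbiota less diverse and dominated by" Enterobacteriaceae. The section on the pathogenesis of NEC presents a more diverse microbiome as the route to prevention.

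**The concern.** Stool from an infant being fed the product contains DNA of the fed strains, whether or not they have established themselves. Placebo stool receives none from the study product. Alpha and beta diversity computed on all reads respond to that added material directly. A difference between arms at the day-14 or 34-week sample therefore has at least two possible sources: product in the stool, and a change in the rest of the community. The stated comparison does not separate them.

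This matters because the protocol's rationale rests on a more diverse and better colonised gut, and the Discussion says the microbiome results will help put the main result in context. A report that probiotics diversified the infants' flora could be no more than a re-measurement of what was fed, and it would colour the reading of either a positive or a null primary result.

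**Working it through.** **1. The plan's own figure.** The strain counts in {6b} add up to the stated dose: 300 + 350 + 350 = 1,000 million. The product profile is therefore q = (0.30, 0.35, 0.35).

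**2. Which samples are affected.** The second sample is labelled as a gestational age, which cannot be meant literally. It is read here as about day 14 of life.

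| Sample | Relation to dosing |
|---|---|
| Around inclusion | Essentially before product |
| About day 14 | Within the dosing period, though some infants may not have started or may be paused |
| 34 weeks ± 2 days | From two days before to two days after the planned end of dosing |
| 12 months corrected age | Long after dosing |

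**3. Mixing model.** Let r be the resident profile, unchanged by treatment, and f the product's share of reads. The stool profile is (1 − f)·r with f·q added. Neither f nor r is in the documents, so both are assumptions and are shown over a range.

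**4. Beta diversity.** If the fed strains are not already resident, the Bray-Curtis distance between this stool and the same flora without product is ½[f + f] = f. It exceeds zero for any f > 0 and is small when f is small.

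**5. Alpha diversity (Shannon).** With no overlap between product and resident taxa,

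H(mix) = (1 − f)·H(r) + f·H(q) + h(f), where h(f) = −f ln f − (1 − f) ln(1 − f) and H(q) = 1.10.

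Example: for r = 0.80 and four taxa at 0.05, H(r) = 0.78. At f = 0.10, H = 0.9 × 0.778 + 0.1 × 1.096 + 0.325 = 1.13, a rise of 0.36.

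| Resident flora (assumed) | H(r) | Change at f = 0.10 | f = 0.50 | f = 0.70 | f = 0.90 | Index falls above |
|---|---|---|---|---|---|---|
| Dominated: 0.80 and 4 × 0.05 | 0.78 | +0.36 | +0.85 | +0.83 | +0.61 | no share tried |
| Moderate: 0.40/0.20/0.15/0.10/0.10/0.05 | 1.58 | +0.28 | +0.45 | +0.27 | −0.11 | about 0.85 |
| Even, ten taxa | 2.30 | +0.20 | +0.09 | −0.23 | −0.76 | about 0.57 |

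At small shares a slightly different dominated flora (0.80/0.10/0.05/0.05, H = 0.71) gives 0.81 at f = 0.02, 0.93 at 0.05 and 1.07 at 0.10.

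**6. Genus-level counting.** Take r = 0.50/0.20/0.15/0.10/0.05, with the last two entries Bifidobacterium and Streptococcus, and add the product as 0.65/0.35 to those two. Richness does not change. Shannon changes by +0.17 at f = 0.30, −0.04 at 0.70 and −0.37 at 0.90.

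**7. Could a test pick this up?** This is an illustration only, because the article names no alpha index and no test for this aim. Resident profiles were drawn from a Dirichlet distribution (mean 0.80/0.10/0.05/0.05, concentration 4), with 100 infants per arm, a two-sided 0.05 test of mean Shannon and no true change in resident flora.

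| Active-arm infants carrying product | f = 0 | f = 0.02 | f = 0.05 |
|---|---|---|---|
| All | 5% reject | 75% | about 100% |
| 70% | n/a | 45% | 95% |
| Half | n/a | about 25% | about 75% |

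**8. Effect of filtering.** Removing the f·q component and dividing by 1 − f returns r exactly. Under an unchanged flora, the Shannon, richness and Bray-Curtis differences all become zero. This requires that product strains can be told from resident ones.

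**The case against.** The strongest objection is that the aim concerns the composition of the microbiome, with no restriction to bacteria other than those fed. Two of the three strains are bifidobacteria, the group whose delayed colonisation the background describes, so finding them in active-arm stool is part of the intended effect. The randomised all-reads contrast is then a legitimate total effect. This stands, and it is why that comparison should be kept. It does not license reading the total effect as a change in the rest of the flora.

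Second, a reader might infer that passage of the product alone must raise alpha diversity, so that the aim is positive by construction. The documents do not support this. The direction depends on the index, the taxonomic level, the resident flora and the product share, and the table above includes falls. Only the beta-diversity separation is general, and only where the fed strains are not already resident.

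Third, a reader might take the whole aim to be compromised. It is not: the inclusion sample is essentially pre-product, and transit cannot explain a difference at 12 months. Late starts and pauses also dilute the effect at day 14.

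Fourth, read filtering may be specified in a full protocol or analysis plan not shown, and section {33} plans complete sequencing with a specialist microbiome centre. Its absence from the article is not the point. The point is that the contrast the article does state cannot, at the on-dose samples, support the mechanism it argues for.

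Last, filtering removes engrafted product strains along with transiting ones. This is correct and limits what the filtered version can show.

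**Conclusion.** The point holds for the samples at about day 14 and 34 weeks ± 2 days. There the stated comparison combines product in the stool with any change in the rest of the flora. Where the fed strains are not already resident, beta diversity separates the arms by the product share alone. Alpha diversity is also distorted: upward at every share tried in the dominated, low-diversity flora that the background describes, but possibly flat or downward with a diverse flora, a high share or genus-level counting.

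The size in this trial is unknown, because the product share is not in the documents. All Shannon values and rejection rates above rest on assumed shares and floras, and the rejection rates also on an assumed test, sample size and between-infant variation. The dose, the dosing period and the sampling times come from the article.

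This is a worthwhile, inexpensive improvement to a secondary aim. The primary analysis is unaffected.

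**What to change.** In Statistical methods {20a}, Secondary aim 6:

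- Keep the all-reads alpha- and beta-diversity comparison, described as the total effect on composition.
- For the two on-dose samples, add the same comparison after removing reads assigned to the three product strains (their species, if strains cannot be resolved) and renormalising. Base statements about the rest of the flora on this version.
- Report product-strain relative abundance as a separate result.
- Base statements about lasting change, or about persistence of the product strains, on the 12-month sample.

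The cost is a few lines of text and one re-run on data already sequenced. The downside is that filtering also removes native members of those species and any engrafted product strains. Both versions must therefore be reported, and the filtered one must not be read as a test of colonisation by the product.

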#### Tertiary aims 1–2

The effect on feeding tolerance (tertiary aim 1) and postnatal growth (tertiary aim 2) will be analyzed using standardized logistic regression and linear regression models.

### Interim analyses {21b}

The DSMC will carry out interim analysis based on a Pocock boundary for safety and efficacy analyses at the time points when 1/3 (*n*=540), 2/3 (*n*=1080), and 3/3 (*n*=1620) of patients have been included. All interim analyses will use the same method as described for primary aims and secondary aims 1-3. A two-sided *p*-value of 0.02205 will be considered significant evidence of the effect of the intervention for the first interim analysis, 0.3794 for the second, and 0.05 at full information accrual.

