## Methods: participants, interventions, and outcomes

### Study setting {9}

We will include 1620 extremely preterm infants at gestational age 22 weeks + 0 days to 27 weeks + 6 days. The infants will be recruited between approximately December 2022 and July 2026 or until enough participants have been included.

Infants will be recruited at six university hospitals in Sweden (Karolinska University Hospital, Skåne University Hospital, Sahlgrenska University Hospital, Linköping University Hospital, Uppsala Univesity Hospital, and Umeå University Hospital), and four university hospitals in Denmark (Rigshospitalet Copenhagen/Glostrup, Aarhus University Hospital, Aalborg University Hospital, and Odense University Hospital).

A sub-study conducted on the sub-cohort will be performed to assess feeding tolerance and postnatal growth. Infants recruited at Karolinska University Hospital will be included in this extended analysis.

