### Outcomes {12}

Table 1 (complete cohort) and 2 (sub-cohort) include descriptions of primary, secondary, and other outcomes including analysis metric, method of aggregation and time points for outcome collection in the PEPS trial. Details of NEC and LOS will be collected for validation of diagnoses and understanding of disease events. Serious adverse events (SAE) will be collected for interim analysis. All covariates collected in the trial are relevant for analyzing the risk of developing the primary and secondary outcomes and will primarily be used for sensitivity analysis.

**Table 1 Tab1:** Description of outcomes with analysis metric, aggregation method, and time points in main cohort

Outcome variables complete cohort			
*Primary outcome variables*	*Analysis metrics*	*Method of aggregation*	*Time point*
Necrotizing enterocolitis	Incidence rate	Mean/Median	During study intervention (until 34 weeks of gestational age)
Necrotizing enterocolitis Bell Stage >II^a^ Verified	Incidence rate	Mean/Median	During study intervention (until 34 weeks of gestational age)
Necrotizing enterocolitis Bell Stage >III^a^ Verified	Incidence rate	Mean/Median	During study intervention (until 34 weeks of gestational age)
Necrotizing enterocolitis Operation	Date, time	Mean/Median	During study intervention (until 34 weeks of gestational age)
Abdominal symptoms	Incidence of free gas, intermural intestinal gas, inflated abdomen discolored abdomen, stagnant intestinal loop >24 h	Sum	During study intervention (until 34 weeks of gestational age)
Differential gastrointestinal diagnoses	Spontaneous intestinal perforation, Malrotation/volvulus, other	Sum	During study intervention (until 34 weeks of gestational age)
X-ray of the abdomen	Incidence rate	Mean/Median	During study intervention (until 34 weeks of gestational age)
Death	Incidence rate	Mean/Median	Third day postpartum until 40 weeks of gestational age

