### Sample size {14}

The sample size calculation is based on the Swedish average incidence of NEC and mortality in extremely preterm infants, which is comparable for Denmark. During the first two to three postnatal days before the intervention is started, the mortality rate is highest among extremely preterm infants. We will calculate the mortality rate from the start of the third postnatal day, as this is the estimated time the enrolled infants will be exposed to the intervention. Based on pooled incidence rate data from SNQ data from the years of 2019, 2020, and 2021, we considered an 18% base rate of the composite outcome NEC and/or mortality, with an estimated 9% overlap. We estimated a 30% reduction, as this was considered clinically relevant and was also the NEC risk reduction rate seen in the ProPrems trial [6]. After analyzing the relative risk for the power analysis, assuming a significance level of 0.05 and 30% reduction rate with interim analysis based on a Pocock boundary at 1/3, 2/3s, and 100% of the information, the proposed enrollment of 1620 patients will have sufficient power [7] to test our hypotheses. Patient enrollment will continue until this number has been reached. Assuming an 80% consent rate, we expect to enroll 1620 infants in 3 years and 8 months.

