## Data collection and management

### Plans for assessment and collection of outcomes {18a}

Outcome variables will mainly be collected from SNQ for the Swedish NICUs and from the Danish Newborn Quality Database (DNQD) for the Danish NICUs. Data not collected from the registries will be retrieved from patient records and collected in an electronic case report form (eCRF) documented in the electronic data capture application, REDCap. A complete list of data that will be documented in REDCap is found in Additional file 1.

The following variables will be documented in the eCRF:Date of randomizationGroup assignmentDate of start of interventionDate of pause of interventionInfection during pregnancyAntenatal antibioticsIf stool samples were taken (at baseline, 14 days post menstrual age (PMA), 34 weeks PMA, and 12 months corrected age)

Only verified NEC and culture-proven LOS will be used for the analysis. For NEC, this is defined as Bell Stage II-III; Bell Stage I will not be considered. Patient records will be used to exclude or add potential NEC (Bell Stage II-III) as a compliment to the SNQ and DNQ registry. The PI of each site is responsible for validating NEC and LOS diagnoses. All validation of NEC and LOS diagnoses will be made prior to unblinding at the end of study period. Validation will be documented in REDCap. All cases of NEC will be reviewed by an external expert group not involved as a researcher in the PEPS trial. This group will consist of at least two experienced neonatologists and one radiologist.

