#### Reporting serious adverse events

All SAEs will be recorded in the eCRF and do not need to be documented immediately. However, to be able to carry out interim analyses, all SAEs must be documented no later than 2 weeks after the intervention has ended for each patient.

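### The two interim looks are timed by inclusion of 540 and 1080 infants, before the primary outcome of the most recent infants is complete or their NEC validated

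*Protocol article*

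**What the plan says.** All places are in the protocol article.

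- **Trigger.** Interim analyses {21b} has the DSMC analyse safety and efficacy when 1/3 (n = 540), "2/3 (*n*=1080), and 3/3 (*n*=1620) of patients have been included", with the method of the primary analysis. Under Statistical methods {20a} that is intention to treat on all randomised infants. Study setting {9} uses the same verb for enrolment: "We will include 1620 extremely preterm infants at gestational age 22 weeks + 0 days to 27 weeks + 6 days". Enrolment is within 72 h of birth (Eligibility criteria {10}).
- **Information.** Sample size {14} bases the power calculation on a Pocock boundary at one third, two thirds and all of the information.
- **Outcome windows.** Outcomes {12}, Table 1, gives the NEC window as "During study intervention (until 34 weeks of gestational age" and the death window as "Third day postpartum until 40 weeks of gestational age".
- **Interim data flow.** So that interims can be run, Reporting serious adverse events states that "all SAEs must be documented no later than 2 weeks after the intervention has ended for each patient". The intervention ends at 34 weeks, so this deadline is about 36 weeks. NEC and death are among the SAEs.
- **Validation.** Section {18a} admits only verified NEC (Bell stage II–III) to the analysis, requires external expert review, and sets one deadline: "All validation of NEC and LOS diagnoses will be made prior to unblinding at the end of study period".

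**The concern.** A count of included infants equals the same fraction of information only if the outcome is known at inclusion. Here the death window closes 12 to 18 weeks after birth. If the rule is followed as written, the most recent infants enter the intention-to-treat denominator with part of their risk period unobserved; they are either missing or counted as event-free so far. The interim reporting deadline does not close the gap, because it falls about four weeks before the death window ends. Nor does anything stated ensure that NEC cases are verified by then, although only verified cases may be analysed.

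These looks can stop the trial, and a Pocock boundary makes an early stop comparatively easy. At stake is a stop, or a decision to continue despite harm, that rests on fewer events than planned and on NEC cases that expert review might later add or remove.

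**Working it through.** **Inputs from the documents.** 1620 infants; "we expect to enroll 1620 infants in 3 years and 8 months", that is 44 months; gestational age at birth 22+0 to 27+6; windows to 34 and 40 weeks; control risk 18%; relative reduction 30%, giving 12.6%; two-sided 0.05; 1:1 allocation; three looks.

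**Assumptions that the documents do not state.** Constant accrual; data cut on the day of the triggering inclusion; lag counted from birth; power of 80% (the protocol gives no figure).

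**1. The plan's own figure.** A fixed design for 18% vs 12.6% at 80% power needs 697 per arm, 1394 in total. Multiplied by the usual Pocock inflation for three looks, about 1.166, this gives 1394 × 1.166 ≈ 1625, against 1620 stated. The constant Pocock critical value z = 2.2895 has nominal p = 0.02205, the value printed for the first look. The sample size therefore fits a three-look Pocock design with equally spaced information.

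**2. Accrual.** 44 months = 191.3 weeks; 1620 / 191.3 = 8.47 infants per week.

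**3. Lag to closure of the death window.** Birth at 27+6: 12.14 weeks. Birth at 22+0: 18 weeks. Midpoint: 15.07 weeks.

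**4. Open death windows at a look** = 8.47 × lag.

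| Lag (weeks) | Open | Share of 540 | Share of 1080 |
|---|---|---|---|
| 12.14 | 103 | 19.0% | 9.5% |
| 15.07 | 128 | 23.6% | 11.8% |
| 18 | 152 | 28.2% | 14.1% |

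**5. Infants with closed windows, as a fraction of 1620.**
- First look: (540 − 152)/1620 = 0.24 to (540 − 103)/1620 = 0.27, instead of 0.33.
- Second look: (1080 − 152)/1620 = 0.57 to (1080 − 103)/1620 = 0.60, instead of 0.67.

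**6. Other cut-offs at the first look.**
- NEC window alone (lag 6.14 to 12 weeks): 52 to 102 infants, 9.6–18.8%.
- Before the 36-week reporting deadline (lag 8.14 to 14 weeks): 69 to 119 infants, 12.8–22.0%.
- Lag counted from randomisation four days after birth: 18.1–27.3% with an open death window.
- Assumed linear ramp-up of accrual over 6 or 12 months: 20–30% or 22–33%.

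**7. Consequence for the first look.** The standardised difference at full information is 0.054 / √[(0.18 × 0.82 + 0.126 × 0.874)/810] = 3.03. First-look power ≈ Φ(3.03 × √(information fraction) − 2.2895).
- 540 complete infants: 3.03 × √0.333 = 1.75; power 29%. Expected events 540 × 0.153 ≈ 83.
- 437 complete: 3.03 × √0.270 = 1.57; power 24%. Events ≈ 67.
- 388 complete: 3.03 × √0.239 = 1.48; power 21%. Events ≈ 59.

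**8. Consequence for the whole design** (simulation, z = 2.2895 at all three looks).

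| Information fractions | Type I error | Overall power |
|---|---|---|
| 0.333 / 0.667 / 1 | 5.0% | 80.1% |
| 0.270 / 0.603 / 1 | 5.2% | 79.9% |
| 0.239 / 0.573 / 1 | 5.3% | 79.8% |

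**The case against.** The best defence is that the trigger is loosely worded, not wrong. Sample size {14} speaks of information, the SAE deadline shows that the interims are meant to use follow-up data, and no section puts the data cut on the day of the triggering inclusion. A DSMC charter or analysis plan may fix the cut. This softens the percentages, which depend on a same-day cut. It does not remove the conflict: the article states a trigger by inclusion and an information assumption that do not match, and its reporting deadline still precedes 40 weeks.

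Second, 19–28% overstates the unknown outcomes. The ends suppose that every pending infant was born at 27+6 or every one at 22+0, and an infant who has already had NEC or died has a determined composite. Open-window infants also contribute some information, so the fractions in step 5 are lower bounds. This stands.

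Third, death status can come from the registries and patient records, and the end-of-study deadline does not bar earlier NEC validation. Both are true, but neither is required before an interim.

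Fourth, truncation affects both blinded arms alike. That also stands: no directional bias is shown.

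Two stronger readings are tempting. A reader might infer that the final analysis is triggered by inclusion of infant 1620. The same section applies the last threshold at full information accrual, and {18a} puts validation before unblinding, so the documents do not support this. A reader might also infer that the timing seriously inflates type I error; step 8 shows that it does not. The later thresholds printed in {21b} are a separate matter.

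**Conclusion.** The concern holds for the two interim looks. The inclusion trigger, the information fractions, the 40-week death window, the reporting deadline of about 36 weeks and the absence of an interim deadline for NEC validation do not fit together.

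Under constant accrual and a same-day cut, 103–152 infants would have an open death window at each look. The share with an undetermined composite is somewhat lower. The cost in error rates is small: at most about 0.3 percentage points each of type I error and overall power under a constant Pocock boundary. The real cost is a stopping decision with about 59–67 expected events among complete infants instead of 83, on NEC cases that may not be validated, while 100–150 analysed infants have yet to report. This should be settled before the first look.

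**What to change.** Reconcile Outcomes {12}, Sample size {14}, section {18a}, Interim analyses {21b} and Reporting serious adverse events as follows:

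1. Take each interim data cut when the 540th or 1080th randomised infant, and every infant randomised before, has died or reached 40 weeks.
2. Analyse those infants only.
3. Have the external expert group validate their NEC cases before the cut.
4. Require death status to 40 weeks to be entered for the interim, from the registries or patient records.

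This restores the fractions 1/3 and 2/3 that the power calculation assumes, so the sample size need not change. Recomputing the boundary from a spending function is optional, useful only if a look falls at another information level.

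The cost is wording in the protocol and any DSMC charter, NEC review in batches by the same group, and interims about 3–4 months later with some 100–150 more infants enrolled by then. If earlier safety review is wanted, the DSMC's continuing review of reported SAEs and SUSARs is unaffected.
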